# SYNOPSIS

| **Study Title** | Effects of group music interventions for mental health service users on anxiety, depression, social resilience and inflammatory response | |
| --- | --- | --- |
| **Internal ref. no. / short title** | 13/LO/1811 | |
| **Study Design** | Quasi-experimental controlled study | |
| **Study Participants** | Adult mental health service users | |
| **Planned Sample Size** | Experimental: 39 to be recruited  Control: 20 to be recruited | |
| **Planned Study Period** | Recruitment from August 2014, study October 2014-December 2014 | |
|  | **Objectives** | **Endpoints** |
| **Primary** | To reduce anxiety and depression | Psychological scale:  Hospital Anxiety and Depression Scale (HADS) |

# BACKGROUND AND RATIONALE

Worldwide, mental health conditions are the leading cause of disability and, along with substance use disorders, are responsible for more of the global health burden than HIV/AIDS, tuberculosis, diabetes, or transport injuries. In the next 20 years, the global lost economic output as a result of mental health conditions will amount to $16 trillion (Whiteford et al., 2013).

Alongside pharmacological and psychotherapeutic treatments for mental health conditions, psychosocial therapies are increasingly appearing, often as an adjunct to conventional treatment as a way of increasing patients’ involvement in their own mental health, encouraging health-promoting behaviours to enhance recovery, and reducing the load of symptoms. A recent systematic review found 69 psychological studies aimed at enhancing mental health and preventing depression or other mental disorders in those at risk or with sub-clinical symptoms (Forsman, Nordmyr, & Wahlbeck, 2011) with interventions including physical exercise, group support, reminiscence or social activities.

One promising psychosocial intervention, which has been recognised as beneficial for mental health for nearly a century is music (Walk, 1928a, 1928b). Indeed, there is now a large body of literature that has demonstrated improved symptoms and reduced severity of conditions, from depression to schizophrenia, in response to music (Erkkilä et al., 2011; Talwar et al., 2006). However, the majority of previous studies have taken place within specific institutions and used a music therapy model, led by a professional music therapist with specific psychological aims. A much less researched area is whether *general* music making within community settings, not led by therapists, can still enhance the mental health and wellbeing of service users. This is an important topic to explore, as a growing number of organisations in the UK and abroad are developing community music interventions for mental health, including Youth Music UK and the Mental Health Foundation. Research into their efficacy is needed to ascertain whether they have a therapeutic effect and to support the design and implementation of future interventions.

One of the community music interventions growing in popularity for mental health is group drumming, perhaps due to the inclusiveness of drumming circles, lack of fine motor skill requirements and strong steadying rhythms. We conducted a preliminary study that explored whether group drumming sessions across six weeks could enhance indicators of mental health (Fancourt et al., In press). Our results showed significant improvements in standardized, self-report measures of depression, social resilience and mental wellbeing among participants. However, this previous study was uncontrolled. Consequently, this planned study seeks to expand on the previous study with a quasi-experimental controlled design.

# OBJECTIVES AND OUTCOME MEASURES/ENDPOINTS

| **Objectives** | **Outcome Measures/Endpoints** |
| --- | --- |
| **Primary Objective** To assess the impact of group drumming on anxiety and depression in mental health service users | Hospital Anxiety and Depression Scale (HADS) |
| **Secondary Objectives**  To assess the impact of group drumming on:  Wellbeing  Social resilience  Psychological stress  Neuroendocrine stress  Inflammatory immune response  To compare whether 6 or 10 weeks is more effective | Warwick-Edinburgh Mental Wellbeing Scale (WEMWBS)  Connor-Davidson Social Resilience Scale (CD-RISC)  Perceived Stress Scale (PSS  Cortisol (through saliva samples)  Cytokines (through saliva samples)  Comparison of results between baseline and week 6 and week 10 |

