# STATISTICS AND ANALYSIS

## Description of Statistical Methods

Data will be analysed using IBM SPSS Version 22.0.1 (SPSS, Chicago, IL). We will compare results using repeated measures analysis of variance (ANOVAs) with planned simple contrasts, both within and between subjects. Differences with a resultant p value of <.05 will be considered significant. In the event that data is non-parametric, we will use Kruskall-Wallis one-way analysis of variance. However, if biological data is non-parametric, we will attempt to transform prior to analysing parametrically.

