## The Number of Participants

Sample size calculations using an alpha of 0.05, power of 0.8 and an effect size of 0.25 (2 groups, 3 timepoints) suggest an overall total of 28 participants will be required (14 per group). For the control group, in order to allow for drop-outs of 30%, 20 participants will be targeted for recruitment. For the experimental group, because of the range of biological markers being tested, we will match sample size with our preliminary study, and so 39 participants will be recruited. Recruitment will be continued until these targets are reached before being closed one week before the drumming starts.

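### The primary objective covers anxiety and depression, but no rule says which HADS score decides it; testing each at .05 and claiming either gives up to 9.75% false claims, not 5%

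*Protocol*

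**What the plan says.** Section 3 gives the primary objective as "To assess the impact of group drumming on anxiety and depression in mental health service users", and the synopsis words it as "To reduce anxiety and depression". In both places the endpoint is the HADS instrument by name and nothing more. There is no statement on total score versus separate anxiety and depression scores, and none on whether an effect on one is enough.

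Section 8.1 plans "repeated measures analysis of variance (ANOVAs) with planned simple contrasts, both within and between subjects" and then sets one rule for all results: "Differences with a resultant p value of <.05 will be considered significant". It gives no order of testing and no adjustment.

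Section 8.2 sizes the study from "alpha of 0.05, power of 0.8 and an effect size of 0.25 (2 groups, 3 timepoints"), which is one test at .05. The result is 28 participants, 14 per group. Recruitment targets are 20 controls (allowing for 30% drop-out) and 39 experimental participants (matching the preliminary study).

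The background reports that the preliminary study found "significant improvements in standardized, self-report measures of depression, social resilience and mental wellbeing among participants". Depression is in that list and anxiety is not.

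**The concern.** HADS can yield an anxiety score, a depression score or a total. The objective names two constructs, and the only decision rule in the protocol treats every difference below .05 as significant. Read literally, that rule lets a significant result on either score stand as a primary finding, although the sample size and the nominal error rate belong to a single test.

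The stake is the error rate of the main claim. With the primary variable open, the choice between total, either score or both scores can be made once the results are known. The preliminary study reported improvement in depression without listing anxiety, so a split result is a realistic prospect here.

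**Working it through.** **Inputs.** From the protocol: alpha .05, power 0.8, effect size 0.25 (read as Cohen's f), 2 groups, 3 timepoints, N = 28, recruitment 39 + 20, 30% drop-out stated for controls. Assumed, because the protocol does not give them: within-person correlation 0.5 between repeated measures, sphericity, two-sided tests, the correlation r between the two HADS tests (shown as a range), and 30% drop-out in the experimental arm as well.

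**Step 1: reproduce the stated sample size.** For the group x time term with m = 3 timepoints, the noncentrality is λ = f² · N · m / (1 − ρ), with degrees of freedom 2 and 2(N − 2).
- N = 28, ρ = 0.5: λ = 0.0625 × 28 × 3 / 0.5 = 10.5, df 2 and 52.
- Power at .05 = 0.812, and 28 is the smallest even N that reaches 0.80. The stated figure reproduces, for one test.
- Controls: 14 / 0.7 = 20, as stated.

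**Step 2: false-positive chance under each reading, with no true effect on either score.**
- One test of the HADS total: 5%.
- Both scores must be significant: at most 5%. In simulation at 39 v 20 with r = 0.6 it was about 1%.
- Either score counts, independent tests: 1 − 0.95² = 0.0975.
- Either score counts, correlated tests: 1 − P(|Z1| < 1.96 and |Z2| < 1.96) for a bivariate normal with correlation r:

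| r | Chance of at least one false claim |
|---|---|
| 0 | 9.75% |
| 0.4 | 9.3% |
| 0.5 | 9.1% |
| 0.6 | 8.8% |
| 0.7 | 8.4% |
| 0.8 | 7.8% |
| 0.9 | 7.0% |

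Simulating the two group x time F tests themselves (39 v 20, 40,000 runs) gave 9.2%, 8.8% and 8.5% at r = 0.5, 0.6 and 0.7, in line with the table.

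**Step 3: what a first threshold of .025 costs.**
- At N = 28: λ = 10.5 as above; power 0.812 at .05 and 0.721 at .025. Reaching 80% at .025 takes N = 34 in equal groups.
- Completers if 30% drop out of both arms: 39 × 0.7 = 27.3 and 20 × 0.7 = 14, so about 27 + 14. The equal-groups equivalent is 4 × 27 × 14 / 41 = 36.9.
- λ = 0.0625 × 36.9 × 3 / 0.5 = 13.8, df 2 and 78; power 0.915 at .05 and 0.859 at .025.
- These depend strongly on ρ. At ρ = 0.3 the same formula at N = 28 gives 0.661 and 0.547; at ρ = 0.7 it gives 0.962 and 0.929.

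**Step 4: power if both scores must pass.** With single-outcome power of about 0.913 to 0.915 at 27 + 14, the bivariate normal gives joint power of about 0.85 to 0.87 for r = 0.4 to 0.7. At N = 28 (0.812 each) it is 0.69 to 0.73.

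**The case against.** The best reply is that the inflated rate is conditional. It needs two separately tested scores, a rule that either is enough, and a correlation the protocol does not give. The objective joins the two constructs with 'and' and names one instrument, so a total score or a both-required rule is a fair reading, and each holds 5%. That stands: 8-9% is not a fixed property of this plan, and a reader who infers that it is goes beyond the text.

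Four further inferences are tempting and not supported.
- *A both-required rule would miss 80% power.* That is so only at N = 28. The protocol recruits 39 + 20, and at about 27 + 14 completers joint power is about 85-87%.
- *The background shows that the scores will be tested separately.* It does not name the scale used in the preliminary study or say whether anxiety was measured. It makes a split result plausible and proves nothing about the planned analysis.
- *A HADS total would leave the error problem in place.* It would not. A total driven by one component raises a question of interpretation, not of false-positive rate.
- *The primary test should move to week 10 alone.* Nothing in the protocol requires this. The sample size is for three timepoints, and the power figures above belong to the group x time test, not to a single-visit contrast.

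It can also be said that scoring and multiplicity methods are commonly left to an analysis plan, which may exist and is not shown. That is true of the adjustment method. It does not fully answer the point, because the protocol itself fixes the p<.05 rule for every difference, and that rule, applied to two primary scores, produces the excess.

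**Conclusion.** The concern holds in a limited form. The protocol names two constructs in its primary objective, leaves the HADS variable open, and applies one unadjusted threshold to every difference. If each HADS score is tested at .05 and either is claimed, the chance of a false primary claim is at most 9.75%, and about 8-9% for an assumed correlation of 0.4 to 0.7, against a nominal 5%. Other readings keep the error at 5% or below. The defect is that the stated rule permits the inflated reading and nothing excludes it. The sample size of 28 is correct on its own inputs; it covers one test at .05. The point concerns only the two scores inside the primary endpoint, not the secondary scales or biomarkers.

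**What to change.** In sections 3 and 8.1, name HADS anxiety and HADS depression as the two primary outcomes, each tested by the group x time term of the planned repeated measures ANOVA. Apply Holm's procedure across the two: the smaller p value against .025 and, if it passes, the other against .05. State that an effect on both anxiety and depression is claimed only if both pass, and that otherwise only the outcome that passed is named. Naming the HADS total as the single primary variable, or requiring both scores at .05, would also hold 5%; Holm is preferred here because it allows a properly controlled claim on one score alone.

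The cost is wording and a stricter first threshold, with no extra participants. Under f = 0.25, ρ = 0.5 and sphericity, power for the test held to .025 goes from about 91% to 86% at 27 + 14 completers, where the 27 assumes that the control arm's 30% drop-out also applies to the experimental arm. At the stated minimum of 28 it goes from 81% to 72%, so the change relies on recruitment reaching its targets.

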# STUDY DESIGN

This will be a quasi-experimental controlled study.

# Study Participants

## Inclusion Criteria

Adults of either gender accessing mental health services.

## Exclusion Criteria

The participant may not enter the study if ANY of the following apply:

- Serious mental health problems which might prevent an individual giving informed consent
- Total deafness or severely impaired hearing
- A dementia that would prevent informed consent
- A physical impairment that would prevent participation in the intervention
- A change in care over the course of the 10 weeks of study e.g. commencing a new/different therapy
- A change in medication over the course of the 10 week study
- A new diagnosis over the course of the 10 week study

For saliva samples:

- Use of medication that might affect saliva samples
- Gum disease that might cause local inflammation of the mouth

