## Screening and Eligibility Assessment

Participants will approach the study team directly if they are interested in taking part in the study. Eligibility criteria will be checked and, if eligible, participants will be sent information sheets and consent forms.

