## Subsequent Assessment

The data collection carried out in week 1 will be repeated in weeks 6 and 10. For the experimental group, this will also be repeated 3 months following the end of the intervention.

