## Withdrawal

If a participant withdraws from the study, data already collected with consent will be retained and used in the study. But no further data will be collected or any other research procedures carried out on or in relation to the participant.

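### Three exclusion criteria rest on events during the 10 weeks that cannot be known at screening; applied after entry, they leave the HADS comparison open to outcome-related selection.

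*Protocol*

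**What the plan says.** Protocol section 5.2 opens its list with "The participant may not enter the study if ANY of the following apply". Three of the items that follow are events in the study period itself:

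- The first of these concerns treatment received: "A change in care over the course of the 10 weeks of study e.g. commencing a new/different therapy".
- The next deals with prescribed drugs: "A change in medication over the course of the 10 week study".
- The last turns to the participant's condition: "A new diagnosis over the course of the 10 week study".

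Section 6.4 fixes when the list is applied: "Eligibility criteria will be checked and, if eligible, participants will be sent information sheets and consent forms". That precedes consent and the first assessment.

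The primary objective in section 3 is "To assess the impact of group drumming on anxiety and depression in mental health service users", measured by HADS. On follow-up, section 6.6 states: "The data collection carried out in week 1 will be repeated in weeks 6 and 10". Section 8.1 plans repeated measures ANOVA within and between subjects, and section 8.3 adds change from baseline.

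Section 6.7 deals with participants who withdraw: "data already collected with consent will be retained and used in the study", and nothing further is collected from them. It does not mention someone who meets an exclusion criterion after entry.

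**The concern.** A criterion for entry has to be decidable at entry, and these three are not. Read literally, they act on people who are already enrolled and have already given baseline data.

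The events are also not neutral with respect to the endpoint. In adults using mental health services, a new therapy, a changed prescription or a new diagnosis may well follow a change in anxiety or depression. Leaving those people out selects the sample on a post-baseline consequence of the outcome. If worsening is the main trigger, the participants who remain look better than the group that was enrolled.

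The planned within-group comparisons are exposed even when both arms lose the same kind of participant. The between-group comparison is exposed if the arms lose participants at different rates or for different reasons. Equal loss cannot be presumed: the study is quasi-experimental (section 4), and the controls are people already attending community social groups (section 7).

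**Working it through.** **1. Can the criteria be applied when the protocol applies them?** Eligibility is checked before consent (6.4). The three events occur during the following 10 weeks (5.2). No section limits them to changes already planned at screening. At screening they can exclude at most a foreseen change; any other change can be acted on only after entry.

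**2. Does another section settle what happens then?** Section 6.7 covers withdrawal only. If a participant with a care change were treated as withdrawn, later HADS scores would not be collected. A repeated measures ANOVA over three timepoints ordinarily uses complete cases, so that person would drop out of the analysis anyway. Removal by the team and treatment as a withdrawal therefore lead to the same selection.

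**3. The plan's own figures.** Section 8.2 gives 28 participants (14 per group) for alpha 0.05, power 0.8, effect size 0.25, 2 groups and 3 timepoints. Reading 0.25 as Cohen's f, and assuming sphericity and correlation 0.5 (neither is stated), the within-between interaction has noncentrality 0.25² × 28 × 3 / (1 − 0.5) = 10.5 on 2 and 52 degrees of freedom. Power is 0.812, so 28 reproduces. For controls, 14 / (1 − 0.30) = 20 also reproduces. The point does not dispute these figures.

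**4. Size of the selection effect in one arm.** All inputs in this step are assumptions; the protocol gives none of them.

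- True mean change is zero; HADS is in SD units; the correlation ρ between any two timepoints is 0.5 or 0.7.
- A participant whose week-6 score is worse than baseline by more than 0.5 SD is removed with probability e = 0.30 or 0.50; anyone else with probability 0.05.

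The week-6 change D is normal with mean 0 and SD s = √(2(1 − ρ)). With p = 1 − Φ(0.5/s):

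- fraction removed: x = 0.05 + (e − 0.05)p
- mean week-6 change in those kept: −(e − 0.05) · s · φ(0.5/s) / (1 − x)
- mean week-10 change: half of that, because the regression of the week-10 change on D has slope (1 − ρ) / (2(1 − ρ)) = 0.5

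For ρ = 0.5: s = 1, p = 0.3085, sφ = 0.3521. For ρ = 0.7: s = 0.7746, p = 0.2593, sφ = 0.2509.

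| ρ | e | Removed | Week 6 (SD) | Week 10 (SD) |
|---|---|---|---|---|
| 0.5 | 0.30 | 12.7% | −0.25 × 0.3521 / 0.873 = −0.101 | −0.050 |
| 0.5 | 0.50 | 18.9% | −0.45 × 0.3521 / 0.811 = −0.195 | −0.098 |
| 0.7 | 0.30 | 11.5% | −0.25 × 0.2509 / 0.885 = −0.071 | −0.035 |
| 0.7 | 0.50 | 16.7% | −0.45 × 0.2509 / 0.833 = −0.135 | −0.068 |

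Simulation gives the same values to within 0.001 SD.

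**5. A second model, in HADS points.** Assume SD 4, ρ = 0.5 (so the change also has SD 4) and no true change. Remove the top fraction q of a score that correlates r with worsening. The mean change in those kept is −4r · φ(z) / (1 − q), where z is the upper-q normal quantile.

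- q = 10%: −0.23 (r = 0.3) to −0.55 (r = 0.7)
- q = 20%: −0.42 to −0.98
- q = 30%: −0.60 to −1.39
- r = 0: no bias at any q

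**6. Between arms.** In the second model, equal removal gives a difference of 0. Removing 30% of the experimental arm and 10% of controls gives −0.36 to −0.85 points (experimental minus control). Removing 10% and 20% respectively gives +0.19 to +0.43. The sign depends on which arm loses more.

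In the model of step 4, if one arm is at e = 0.50 and the other at e = 0.30, the week-6 difference is 0.195 − 0.101 = 0.094 SD at ρ = 0.5 and 0.135 − 0.071 = 0.064 SD at ρ = 0.7. For scale, 30% loss from 39 and 20 leaves about 27 and 14. The standard error of the difference in change is then s√(1/27 + 1/14), which is 0.33 SD at ρ = 0.5 and 0.26 SD at ρ = 0.7.

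**The case against.** The best counter-argument is that removal is inferred. No section says that enrolled participants will be dropped or their data deleted. The wording of the list heading and the pre-consent check also allow a screening reading, under which people with a change already in prospect are simply not enrolled. Analysis populations are commonly left to a SAP, which is not shown here. This stands as far as it goes: removal is the natural reading of a criterion that can be met only after entry, but it is not stated text. It does not remove the point, because the ambiguity lies in an eligibility rule that the protocol itself fixes.

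Second, the protocol provides no way of detecting the events. The repeated assessments contain no item on care, medication or diagnosis; medical records are not accessed (9.2); and health professionals pass on no personal information (6.1). The assumed 30–50% removal of worseners therefore has no basis in the document. That is right, and it is why the figures are only an illustration. Reliance on volunteered reports also gives no assurance that the rule would be applied alike in both arms.

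Third, limiting co-intervention is a legitimate aim. In a non-randomised comparison, care changes that are kept in and differ between arms could produce a systematic difference and not just noise. This stands and belongs in the cost of the fix.

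A reader might also infer three stronger things that the protocol does not support:

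- **That HADS change is biased, and in a favourable direction.** Size and sign depend on how closely removal tracks HADS, whether improvers are removed too (for example after medication is stopped), and whether the arms differ. None of this is given.
- **That section 6.7 contradicts section 5.2.** It covers withdrawal and is silent on this case.
- **That the exclusions use up the 30% drop-out allowance.** The illustrated 11–19% is below 30%. The allowance is stated for controls only, and the experimental arm recruits 39 against 14 required. What can be said is that no separate allowance exists: if ordinary drop-out took the full 30%, a further 11–19% would leave about 11 to 12 of the 14 controls (14 × 0.811 = 11.4; 14 × 0.885 = 12.4).

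**Conclusion.** The point holds in a conditional form. Three criteria in section 5.2 cannot be assessed when section 6.4 applies them, and no other section limits them or says what follows when one is met after entry. If they are enforced as written, the sample is selected on events plausibly caused by the primary outcome. The within-group HADS change is then open to bias, and so is the between-group comparison if removal differs by arm.

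The illustrated spurious improvement in a single arm is about 0.07–0.20 SD at week 6 and 0.04–0.10 SD at week 10, with 11–19% removed. These figures rest on assumed one-sided removal, assumed correlations and no true change. Between arms the effect could be zero or of either sign, and in the unequal-removal example it is small beside the standard error. The case for acting is that the rule bears on who counts in the primary endpoint, and that HADS scores not collected after a care change cannot be recovered later.

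**What to change.** - Reword the three items in section 5.2 so that they can be judged at screening: care, medication and diagnosis stable before entry, or no change already planned.
- State that HADS collection continues, and that every enrolled participant stays in the primary analysis, whatever later happens to their care. A participant's own withdrawal of consent remains under section 6.7.
- Add a short item at weeks 6 and 10 recording any change in care, medication or diagnosis.
- Report these changes by arm, and give the analysis restricted to participants without such changes as a sensitivity analysis only.

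The cost is protocol wording, one extra questionnaire item and one extra analysis. There is also a cost in interpretation. The primary estimate will include the effect of any care changes. In a non-randomised comparison these may differ systematically between arms, so the by-arm report is needed to read the result.
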